## Abstract

**Background:**

Beta-lactams (i.e., penicillins, cephalosporins, carbapenems, monobactams) are the most widely used class of antibiotics in critically ill patients. There is substantial interpatient variability in beta-lactam pharmacokinetics which renders their effectiveness and safety largely unpredictable. One strategy to ensure achievement of therapeutic concentrations is drug level testing (“therapeutic drug monitoring”; TDM). While studies have suggested promise with beta-lactam TDM, it is not yet widely available or implemented. This protocol presents a mixed-methods study designed to examine healthcare practitioners’ perspectives on the use and implementation of beta-lactam TDM in the critically ill.

**Methods:**

An explanatory sequential mixed-methods design will be used [QUANT → qual]. First, quantitative data will be collected through a web-based questionnaire directed at clinicians at three academic medical centers at different phases of beta-lactam TDM implementation (not yet implemented, partially implemented, fully implemented). The sampling frame will include providers from a variety of disciplines that interact with drug level testing and interpretation in the critical care environment including pharmacists, intensivists, infectious diseases experts, medical/surgical trainees, and advanced practice providers. Second, approximately 30 individuals will be purposively sampled from survey respondents to conduct in-depth qualitative interviews to explain and expand upon the results from the quantitative strand. Normalization Process Theory and the Consolidated Framework for Implementation Science will be used to guide data analysis.

**Discussion:**

These data will be used to answer two specific questions: “What are ICU practitioners’ perspectives on implementing beta-lactam TDM?” and “What factors contribute to the success of beta-lactam TDM program implementation?” Results of this study will be used to design future implementation strategies for beta-lactam TDM programs in the critically ill.

**Trial registration:**

NCT04755777.

**Supplementary Information:**

The online version contains supplementary material available at 10.1186/s43058-021-00134-9.

Contributions to the literature
Use of implementation science frameworks will evaluate the “work” associated with implementation of beta-lactam therapeutic drug monitoring, and the contextual factors that influence its success.Study is situated in the high-risk intensive care unit environment.Merging and triangulation of quantitative and qualitative strands will identify areas where participants have similar or dissimilar perceptions or practices.Data analysis designed to inform implementation of beta-lactam therapeutic drug monitoring to promote scale and spread.

## Background

Beta-lactams account for at least 70% of the antibiotics utilized in caring for critically ill patients [1]. Inclusive of cephalosporins, penicillins, carbapenems, and monobactams, beta-lactam antibiotics form the backbone of all major treatment algorithms in the critically ill including for undifferentiated sepsis, pneumonia, bacteremia, urinary tract infections, intra-abdominal infections, skin and soft tissue infections, and meningitis [2–6]. Substantial inter- [7, 8] and intra-patient [9] variability in beta-lactam concentrations have been observed in critically ill patients which is thought to contribute to suboptimal effectiveness, safety, and development of antibiotic resistance [10]. For this reason, international guidelines and consensus statements have advocated for the use of novel approaches to personalize beta-lactam therapy including real-time drug level testing (also referred to as “therapeutic drug monitoring” or TDM) [2, 11, 12].

Beta-lactam TDM is designed to optimize the drug level within the therapeutic window to ensure maximal effectiveness and safety. For the beta-lactam antibiotics, achievement of an adequate drug level (fraction of time above the minimum inhibitory concentration of the organism) is associated with a higher likelihood of clinical success [7] and a decrease in the potential for antimicrobial resistance [13]. Conversely, excessive beta-lactam exposure has been associated with an increased risk of concentration-dependent toxicities, most notably neurotoxicity [14–16]. Beta-lactam TDM programs have been used in adult and pediatric critically ill patients. In these studies, when the drug levels were evaluated 2–3 days into therapy (at the assumed pharmacokinetic steady state), 40–90% of patients failed to achieve the desired target beta-lactam levels. The majority of non-target levels were low which underscores the need for therapeutic optimization [17–20].

While TDM for antimicrobials in the critically ill is not new, its application to beta-lactams remains poorly adopted. In a multicenter multinational survey of antimicrobial dosing and monitoring practices in intensive care units (ICUs) in Europe, only approximately 10% of respondents reported use of TDM for piperacillin/tazobactam and carbapenems. When used, it was described as infrequent, and pharmacokinetic/pharmacodynamic targets varied widely across institutions [21]. In a national cross-sectional study about antibiotic TDM practices distributed to physicians in ICUs in Germany, 17% and 22% of respondents reported use of TDM for piperacillin and meropenem [22]. Several possible explanations exist for the limited adoption. One is the relatively limited access to beta-lactam assays (often a send-out test) which results in prolonged turnaround time. Other assays for drugs where TDM is more common are widely available and performed on automated chemistry analyzers with FDA approved assays. There are also limited data that conclusively demonstrate the link between TDM-informed dosing and more favorable clinical outcomes than with standard strategies. Finally, there may be implementation challenges of such a program given the high frequency of beta-lactam use in critically ill patients. TDM has historically been limited to antimicrobials with narrow spectrums of activity (treat only select groups of bacteria), relatively infrequent use, and narrow therapeutic windows (often a high risk for toxicity). Chief among the examples of agents with substantial literature in support of the role for TDM include vancomycin and the aminoglycosides. In the previously mentioned German evaluation, in contrast to the beta-lactams, 75% of ICU practitioners report routine use of TDM for vancomycin [22].

Even with more mainstream antibiotics that undergo TDM, a clear gap in the literature exists surrounding the implementation considerations associated with these TDM programs from the perspective of the end user [23]. Perhaps the closest corollary is the recent effort with vancomycin to characterize implementation of the change from trough- to area under the curve-based monitoring (two different pharmacokinetic targets) [24–26]. Extrapolated from these narrative descriptions, several key factors pertaining to implementation appear important. Implementation includes a series of phases including preparation, go-live, and evaluation, each of which requires careful planning. TDM practices are governed locally by clinical practice groups such as in the intensive care unit, the pharmacy and therapeutics committees, and the antimicrobial stewardship teams. Input from leadership of these groups as well as end-users is necessary to ensure successful implementation. Chief among the factors that appear to most influence implementation of TDM programs is clinician familiarity. Education, training, and real-time support delivered by identified local champions may be used to enhance clinician awareness, knowledge, and confidence. Moreover, proactive attention to logistical issues (e.g., documentation, online resources, electronic health record integration) may facilitate a streamlined and successful implementation experience. Collectively much more information is necessary to better understand how best to efficiently and effectively implement beta-lactam TDM.

This manuscript presents the protocol of a mixed-methods study which aims to characterize the barriers and facilitators for beta-lactam TDM implementation in real-world practice from the perspective of a diverse group of ICU clinicians. At the conclusion of this study, we seek to answer the following two questions:
What are ICU practitioners’ perspectives on implementing beta-lactam TDM?What factors contribute to successful implementation of beta-lactam TDM programs?

## Methods/design

### Overall design

This study will use a two-phase explanatory sequential mixed-methods design to evaluate factors which influence beta-lactam TDM in critical care practice (Fig. 1; QUANT → qual). A mixed-methods design was selected to not only measure provider perspectives on the need for testing but to use first-person accounts to describe perceived barriers and facilitators associated with implementation of beta-lactam TDM. The quantitative strand will be the principal strand and the qualitative strand will be the complementary method. The study was ethically approved by the local Institutional Review Boards and ethics committees prior to beginning enrollment and has been registered at ClinicalTrials.gov (NCT04755777). The design and reporting of this study is informed by best practices for survey research [27, 28], qualitative research [29], and mixed-methods studies [30] (Additional file 1).

**Fig. 1 Fig1:**
[figure not shown]
Study schema

### Survey development

For the quantitative strand, a web-based survey was designed expressly for this study based on previous evidence in the area [21, 24–26] (Additional file 2) in consultation with the local Survey Research Center. Study data will be collected and managed using Qualtrics. Response options for most survey items are close-ended and used statements of agreement and Likert scales.

Seven clinicians (2 intensivists, 3 critical care pharmacists, 1 infectious diseases/antimicrobial stewardship pharmacist, 1 critical care nurse) from diverse hospitals (community and academic) across the USA not involved with the study reviewed and pre-tested the questionnaire. A structured critique form was given to each of these individuals upon survey completion which included specific probes designed to examine question clarity, response options, missing or superfluous survey items, and overall length. Critiques were reviewed and themes identified. Edits were made to questions and responses to address areas of ambiguity. Suggestions about breadth and depth of content resulted in removal of four survey items and addition of eight others. Of these eight additional, seven were open-ended response options from branching logic (e.g., “Please describe your other goal…”). Mean estimated time to complete the survey in pretesting was 8 min.

### Sample

Data will be obtained from ICU clinicians at three hospitals with distinct beta-lactam dosing and monitoring practices.

*Center 1* is a large tertiary referral hospital in Australia. Beta-lactam TDM began at center 1 in 2009 and is *fully implemented* in the routine care of critically ill patients. The hospital offers a variety of acute care services including an active emergency department, intensive care services for 36-ICU beds, and care for hematology/oncology patients including those undergoing hematopoietic stem cell transplantation. 2.25 full time equivalent pharmacists provide a 7-day per week intensive care service that includes pharmacokinetic monitoring of medications. At the outset of the beta-lactam TDM program, the target drug concentration was based on the total drug level, measured as a trough, which targeted a threshold of 4× the minimum inhibitory concentration (MIC) breakpoint of the known or suspected organism. Currently, Center 1 measures free drug concentrations and targets have been tailored to local MIC distributions. Consistently, beta-lactam TDM is performed in ICU patients but has been extended to other services including the outpatient antimicrobial treatment team. Beta-lactam assays are available once daily Monday through Saturday.

*Center 2* is a large university-affiliated academic medical center in the southeast region of the USA which has been performing beta-lactam TDM since 2016 and currently it is considered *partially implemented*. Center 2 offers a wide array of acute care services and has more than 200 ICU beds including medical, surgical, neurological, cardiac, and thoracic and vascular units. There are 11 ICU pharmacists and 3 infectious diseases specialty pharmacists. The antimicrobial TDM is performed by the physicians and pharmacists. It is currently non-protocolized but encouraged for critically ill patients with suspected or documented infections. The recommended approach to beta-lactam TDM is to order peak (1 h after the end of the infusion) and trough samples (30 min prior to the next dose) for each patient. Most often clinically, however, isolated troughs are collected. Once collected, samples are sent to the local pharmacokinetics laboratory which offers LC-MS/MS assays for 11 beta-lactams. Batched beta-lactam assays are performed once daily Monday through Friday. The results are delivered to the electronic health record (Epic) for clinical interpretation and PK/PD calculations.

*Center 3* is a large integrated academic health system in the Midwest region of the USA. Center 3 has developed and validated LC-MS/MS assays for total concentrations of piperacillin, tazobactam, cefepime, and meropenem, but these are *not yet implemented* or available for clinical care. The center includes two hospital campuses at its Midwest location across which there are more than 200 total ICU beds. TDM for antimicrobials and other agents in the ICU are performed by decentral clinical pharmacists for which there are 42 across the two hospitals. Four infectious disease specialty pharmacists also consult on ICU patients. Laboratory facilities to deliver TDM are staffed 24-h/day, 7 days/week. It is expected that when available clinically, the assays will be batched and performed once daily, 7 days/week.

### Phase 1—quantitative strand

#### Data collection

Data will be sourced from a multicenter cross-sectional survey of clinicians working with critically ill patients at the study sites of interest. Healthcare providers from a variety of disciplines interact with drug level testing and interpretation in the critical care environment. Based on our previous experiences with implementing new antibiotic dosing nomograms [31, 32] and the published literature on TDM [24–26], key clinician stakeholders likely to be involved with beta-lactam TDM in the intensive care unit include pharmacists, intensivists, infectious diseases experts, medical/surgical trainees, and advanced practice providers. These individuals will form the sampling frame for the quantitative strand of the mixed-methods study. The objective will be to reflect insights from a range of practitioners including those with considerable experience with routine beta-lactam TDM to those with little or no exposure to it. It would be expected that all of these individuals would have familiarity with antibiotic TDM, in general, but maybe not specific to this drug class.

The study team involves investigators from each participating site. These individuals will be primarily responsible for identifying study participants. To minimize the potential for bias, the questionnaire will be distributed by a survey center independent of the investigative group. Eligible individuals will be contacted via e-mail and invited to participate in the survey. By following the survey link in the structured electronic communication, clinicians will indicate their consent to participate. Reminder communication will occur electronically at 2 weeks and 3 weeks, and the survey will close at the conclusion of the fourth week. Demographic information will be collected including the clinician’s self-reported role on the care team (attending physician, trainee, advanced practice provider, pharmacist), specialty (ICU vs infectious diseases), and years of post-graduate practice experience. To facilitate purposive sampling for the qualitative strand of the study, individuals will be asked to indicate their willingness to be contacted for a future individual interview.

#### Analysis

Based on the mean number of individuals employed at these institutions in the clinical specialties of interest, we expect to administer the survey to approximately 250 individuals at each site (750 individuals total). At each site, we estimate between 5 and 40 individuals are available for sampling in each of the provider subtypes of interest. Recent estimates indicate that physician response rate to surveys approximates 15–20% depending on survey mode [33]. In previous multicenter studies, we observed a response rate between 22 and 47% influenced by clinician subtype [34, 35]. Therefore, we estimate conservatively that 150 individuals will respond to the web-based survey and be eligible for analysis.

Survey response data will be described with frequencies and percentages, and means with standard deviations. Individuals may answer (or not answer) any question on the survey. Missing data will be analyzed for patterns but will not be imputed. The denominator for each survey item will be described. The Pearson’s chi-square test or Fisher’s exact test will be used to analyze independent binary outcomes stratified according to groups (e.g., clinician subtype, level of experience). Survey response rate and results will be compared between the three sites. A *p*-value < 0.05 will be considered statistically significant for these analyses.

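### Role comparisons rest on one-factor tests that, read naturally, pool three centers at different TDM stages, so pharmacist-versus-other contrasts can be partly confounded by site

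*Protocol article*

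**What the plan says.** The Analysis section of the quantitative strand (Protocol article) names the Pearson chi-square test and Fisher's exact test. These "will be used to analyze independent binary outcomes stratified according to groups (e.g., clinician subtype, level of experience"). It adds: "Survey response rate and results will be compared between the three sites". The threshold is a p-"value < 0.05 will be considered statistically significant for these analyses". No site-stratified test is named, and no model with site and role together.

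On size, the same section states that "we expect to administer the survey to approximately 250 individuals at each site (750 individuals total") and that "we estimate conservatively that 150 individuals will respond to the web-based survey and be eligible for analysis". It expects 5 to 40 people per provider subtype at each site, and cites earlier response rates of 22 to 47% that depended on clinician subtype.

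The Sample section gives pharmacist staffing:
- Center 1, fully implemented: "2.25 full time equivalent pharmacists provide a 7-day per week intensive care service".
- Center 2, partially implemented: "There are 11 ICU pharmacists and 3 infectious diseases specialty pharmacists".
- Center 3, not yet implemented: "decentral clinical pharmacists for which there are 42 across the two hospitals", plus four infectious disease pharmacists.

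**The concern.** The centers were selected because their experience with beta-lactam TDM differs, so differences in opinion between sites are something the design looks for. If one role is concentrated at one stage of implementation, an unadjusted comparison of that role with the others carries part of the site difference.

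The practical question is whether pharmacists see TDM differently or mostly work where it is not yet available. The two answers call for different implementation strategies. The quantitative strand is the principal strand of the study, and its results are merged into the conceptual model.

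**Working it through.** **The plan's own figure.** 3 × 250 = 750 invited. At 20% response, 750 × 0.20 = 150, which reproduces the stated number of respondents. No effect size, power or agreement rate is stated, so there is none to reproduce.

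**Inputs from the protocol.** 250 invitees per site; pharmacists 11 + 3 = 14 at Center 2 and 42 + 4 = 46 at Center 3.

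**Assumptions.**
- Center 1 gives full-time equivalents, not heads; 3 pharmacists are assumed.
- As a check inside the stated range of 5 to 40 per subtype, 5/14/40 is also used.
- Agreement by site is 80/60/40% (Centers 1, 2, 3) or, more mildly, 70/60/50%.
- Role has no effect within any site.

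**Imbalance (3/14/46).** Pharmacists at Center 3: 46/63 = 73%. Other clinicians at Center 3: 204/687 = 30%.

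**Pooled agreement** = sum over sites of (number × site rate) ÷ total number in the role.

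| Pharmacists by site | Site rates | Pharmacists | Others | Gap |
|---|---|---|---|---|
| 3/14/46 | 80/60/40% | (2.4 + 8.4 + 18.4)/63 = 46.3% | (197.6 + 141.6 + 81.6)/687 = 61.3% | 14.9 points (before rounding) |
| 5/14/40 | 80/60/40% | (4.0 + 8.4 + 16.0)/59 = 48.1% | (196.0 + 141.6 + 84.0)/691 = 61.0% | 12.9 points |
| 3/14/46 | 70/60/50% | (2.1 + 8.4 + 23.0)/63 = 53.2% | (172.9 + 141.6 + 102.0)/687 = 60.6% | 7.5 points (before rounding) |

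With equal rates at all sites the gap is zero.

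**Rejection rates by simulation** (two-sided 0.05, no role effect within site). The unequal-response case assumes that pharmacists respond at 47%, the top of the cited range, and others at 18 to 20%.

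| Pharmacists by site | Site rates | Unadjusted, 20% response in all roles | Unadjusted, unequal response |
|---|---|---|---|
| 3/14/46 | 80/60/40% | about 15–16% | about 32–33% |
| 5/14/40 | 80/60/40% | about 12% | about 25% |
| 3/14/46 | 70/60/50% | about 7–9% | about 12% |
| 5/14/40 | 70/60/50% | about 6% | about 10% |

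A Cochran–Mantel–Haenszel test stratified by site rejects about 5% of the time throughout.

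**Reverse direction (role contaminating site).** The pharmacist share of invitees is 3/250 = 1.2% at Center 1 and 46/250 = 18.4% at Center 3, a difference of 17.2 points. A role effect of 20 to 40 points with no site effect then gives a spurious site gap of 0.172 × 20 = 3.4 to 0.172 × 40 = 6.9 points at equal response. If pharmacists respond at 47% and others at 18%, the respondent shares are 3.1% and 37.1%, and the gap is 6.8 to 13.6 points.

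**Experience.** The protocol gives no distribution of years of practice by site or role, so confounding by experience cannot be quantified.

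**The case against.** The strongest case against has five parts.

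- **Pooling is not stated.** The groups are given as examples, and the wording does not exclude splitting by role within site. This stands as a limit on certainty. Pooling is the natural reading, because site appears as a separate comparison.
- **The survey is descriptive.** There is no primary hypothesis, effect size or causal claim. Under the assumed rates the marginal percentages really do differ, so a rejection is wrong only as a statement about role within site. This stands and lowers the severity. The marginal figure is nevertheless easily read as a role effect.
- **The staffing counts are not the invitee list.** Center 1 is an ICU service figure with no infectious diseases pharmacists listed, and both 3 and 46 fall outside the stated 5 to 40. This stands. The 5/14/40 check reduces the effect but does not remove it. The imbalance is also documented for pharmacists only.
- **Downstream harm is limited.** Interviewees are chosen for diversity of center, discipline, experience and individual answers, not by role p-values. This stands for interview selection. It does not correct a survey contrast that enters the merged results.
- **An article condenses the full plan.** The article does name its tests and threshold, and the criticism is of the method named.

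A reader might infer that the pharmacist test is essentially Center 3 against the rest, or that the plan is bound to mistake site for role. The figures do not support that. Only 46 of 250 Center 3 invitees (18%) are pharmacists. The correlation between being a pharmacist and being at Center 3 is (46 × 483 − 204 × 17)/√(63 × 687 × 250 × 500), about 0.25. That is partial confounding, and it biases the contrast only if answers differ by site.

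**Conclusion.** The concern holds as partial confounding of pharmacist-versus-other contrasts by site, on the natural reading that role tests combine the centers. The spurious gap is about 13 to 15 points and rejection about 12 to 33% under an assumed 80/60/40% site gradient. Rejection is about 6 to 12% under 70/60/50%, against about 5% with stratification by site. These sizes rest on assumed agreement rates, an assumed Center 1 headcount and, at the upper end, assumed higher response among pharmacists.

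Contamination of site comparisons by role is smaller, clearly so at equal response. For roles other than pharmacist, and for experience, the protocol gives no counts from which to judge. In a largely descriptive survey this is a should-fix, not a defect that invalidates the study.

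**What to change.** For the key items (for example Q14, Q16a and Q16c, already singled out for interview sampling):

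1. Show role results within each site before any pooled figure.
2. Test role with a Cochran–Mantel–Haenszel test stratified by site, or fit one logistic or ordinal model with site and role and report adjusted odds ratios with 95% confidence intervals.
3. Label the unadjusted chi-square and Fisher tests exploratory.

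Only analysis wording changes: role and years of practice are collected, and site is known.

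The cost is precision. With about 150 respondents, sparse roles must be collapsed, adjusted estimates will be imprecise, and a site-by-role interaction is not estimable. Center 1 may contribute few or no pharmacists. With 3 invited and 20% responding, 3 × 0.20 = 0.6 are expected, and the chance of none is 0.8³ = 51%. A stratum without pharmacists adds nothing to the stratified test, and the report should say so if it happens.
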